#### Cost-effectiveness

The cost-effectiveness evaluation will be performed from a societal perspective and includes a cost-effectiveness analysis (CEA) and cost-utility analysis (CUA). The primary clinical outcome for the CEA will be the severity of the BPD manifestations and for the CUA utility scores will be derived from the quality of life instrument(s), both with a time horizon of 12 months after the end of treatment. The net benefit will be used to express cost-effectiveness. For each patient, the net benefit will be calculated by subtracting the costs incurred by the patient from the amount that the society is willing to pay for the health benefit [212]. The development of the net benefit over time and differences between the treatments will be modeled using multilevel modeling in which the hierarchical structure of the data and potential missing values are taken into account. The best fitting model to describe the development over time and the appropriate distribution of the net benefit data (e.g., gamma distribution, log-normal distribution) will be based on the data. Cost-effectiveness acceptability curves (CEACs) will be drawn showing the probability that one treatment is more cost-effective compared to the other treatment, given the observed data, for a range of willingness-to-pay values. Sensitivity analyses will be performed to address the uncertainties in methodology and assumptions and to test for the robustness of findings.

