Several studies have demonstrated the effectiveness and the efficacy of DBT and ST for BPD, although the evidence is mostly based on low-to-moderate-quality evidence, and trials focusing on DBT, but especially ST, are limited [24, 25]. In addition, substantial reductions in direct and indirect healthcare costs have been found for both treatments [26]. However, research on the comparative effectiveness and cost-effectiveness of the two interventions is lacking. Moreover, research on mediators and moderators of treatment effects is limited. This gap warrants attention, as treatment effectiveness can be optimized by identifying mechanisms within treatments that are associated with improvement and patient characteristics that predict (differential) treatment response [27]. Optimizing treatment effectiveness of DBT and ST for BPD is highly needed since a substantial proportion of patients does not respond fully to either DBT or ST. A systematic review found a mean percentage of non-response of 46% among BPD patients treated with specialized psychotherapies, including DBT and ST [28]. In addition, more than one-third of the patients did not achieve a reliable change in BPD symptoms or even showed an increase in BPD severity after DBT or ST [29–31]). Finally, dropout rates up to 30% have been found for DBT and ST [32, 33]. Individual differences in responses to both ST and DBT have been observed across studies, but the factors driving these differences in treatment response among BPD patients are largely unknown. This state of affairs leaves the principal question “What treatment, by whom, is most effective for this individual with that specific problem, under which set of circumstances?” ([34], p111), historically one of the key questions dominating the psychotherapy research agenda, fully open in the treatment of BPD individuals [35, 36]. Identifying factors that specify which patients will benefit most from which treatment (i.e., treatment selection, or also known as precision medicine or personalized medicine; [37, 38]) will lead to fewer mismatches between patients and treatments, and in turn to better outcome and more efficient use of healthcare resources.

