##### Quality of life

Generic quality of life is assessed using the 5-level EuroQol 5D version (EQ-5D-5L; [194]). The questionnaire measures five health state dimensions (mobility, self-care, usual activities, pain/discomfort, and anxiety/depression). Each dimension is divided into five severity levels: no problem, slight problems, moderate problems, severe problems, and extreme problems. The profiles from the five health state dimensions are assigned a value based on the Dutch social tariffs to generate health utilities [195]. These utilities will be used to calculate Quality Adjusted Life Years (QALYs) by multiplying the change in utility values between assessments by the length of the period between assessments. In addition to the five health state dimensions, the EQ-5D-5L contains a VAS item which records the patient’s self-reported health status ranging from 0 (worst health you can imagine) to 100 (best health you can imagine). The EQ-5D-5L has shown to be a reliable and valid measure among different patient groups in different countries [196].

As a complement to the EQ-5D-5L, the Mental Health Quality of Life seven-dimensional Questionnaire (MHQoL-7D; [197]) will be administered. The MHQoL-7D is a recently developed instrument to assess quality of life specifically in people with mental health problems. The MHQoL-7D consists of seven quality of life domains (self-image, independence, mood, relationships, daily activities, physical health, and hope) and a VAS item which records the patient’s self-reported psychological well-being. A study into the psychometric properties of the MHQoL-7D is currently running. The MHQoL-7D will only be included in the analysis if it is demonstrated to be a psychometrically sound instrument and Dutch social tariffs are available.

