### Statistical analyses

The statistical analyses for the (cost-)effectiveness, mechanisms of change and treatment selection studies are under development. For example, according to Cohen et al. [48], the treatment selection field is still in its developmental stage and statistical methods are constantly evolving. Recently, great efforts have been made by several authors (e.g., [205, 206]) to select the optimal prediction model by comparing different variable selection techniques. Considering the ongoing advances in methodological approaches, the statistical analyses described below should be considered as examples of appropriate analytic methods. We will determine the optimal methods at the time of the analyses. An update of the protocol will be published, including the selected statistical methods, before start of the data-analyses. The statistical analyses will be performed according to the intention-to-treat (ITT) principle (i.e., including all patients that have been randomized and received at least one treatment session). In addition to the primary analysis based on the ITT principle, a completers analysis will be conducted by excluding patients who dropped out prematurely (i.e., termination of the treatment before planned end, without patient and therapist agreeing that enough improvement has been reached to justify the termination) or deviated from the protocol (e.g., sought other psychological treatment in addition to the study treatment). No interim analyses are planned.

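### The only example distributions named for net benefit, gamma and log-normal, exclude the negative values that net benefit as defined can take

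*Protocol article*

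**What the plan says.** The Cost-effectiveness section of the protocol article obtains each patient's net benefit by "subtracting the costs incurred by the patient from the amount that the society is willing to pay for the health benefit". Its development over time and the difference between arms are to be analysed by multilevel modelling, and "the appropriate distribution of the net benefit data (e.g., gamma distribution, log-normal distribution) will be based on the data". Acceptability curves are then drawn "for a range of willingness-to-pay values"; no lower or upper limit is given.

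Other sections fix what goes into net benefit:

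- **Benefit.** Under Quality of life, QALYs are obtained "by multiplying the change in utility values between assessments by the length of the period between assessments".
- **Costs.** "The cost-effectiveness evaluation will be performed from a societal perspective", so healthcare, patient and family costs and productivity losses all count.
- **Patients.** The analysis set is defined as "including all patients that have been randomized and received at least one treatment session".

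The opening paragraph of Statistical analyses presents all the methods as illustrations and promises a published update with the chosen methods before analysis starts. No section mentions shifting net benefit, changing its sign, or using the two named families for costs alone. For the clinical outcomes, the Clinical effectiveness section includes the normal distribution among its examples; the list for net benefit does not.

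**The concern.** Net benefit is a difference and can take either sign. Gamma and log-normal are defined only above zero. They are natural candidates for costs, which are positive and skewed, but not for net benefit.

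An analyst who stayed with either family would have to do one of two things:

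- **Drop the negative values.** This removes patients selectively: those with high costs and little or no gain.
- **Add a constant to make all values positive.** The constant is arbitrary. If the shifted values are then logged, the arms are compared on a geometric rather than an arithmetic mean, and the answer depends on the constant. A societal decision needs the arithmetic mean.

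Comparing cost-effectiveness is one of the four primary objectives, and the Treatment selection section carries it into the generalization analyses.

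**Working it through.** The plan gives no costs, QALY values or share of negative net benefits, so there is no figure to reproduce. The check has an algebraic part, which needs no assumption about amounts, and a numerical part, which does.

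**1. Sign of net benefit.** Write NB = W x E - C, where W is willingness-to-pay, E is benefit and C is cost (Cost-effectiveness section). Everyone analysed has had at least one session, so C > 0 over the full horizon.

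- If E <= 0, then W x E <= 0 for every W >= 0, so NB <= -C < 0 at every threshold. With QALYs built on change in utility, E <= 0 is what a patient who does not improve, or worsens, contributes.
- As W approaches 0, NB approaches -C for every patient, whatever E is.
- If E > 0, NB is negative whenever W < C/E.

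**2. Support of the named families.** The log-density of a gamma (shape 2, scale 5,000) and of a log-normal (sigma 1, scale 5,000) is minus infinity at -1 and at -1,000. The same holds at any negative value for any parameters.

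**3. What a fit does.** Assumed: 200 patients, W = EUR 20,000, gamma costs with mean EUR 20,000 and coefficient of variation 1, and normal QALY change with mean 0.5 and SD 0.6. Of the 200 net benefits, 129 had no logarithm. A gamma model with log link stopped with an error.

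**4. How large the share could be.** Costs were assumed gamma with coefficient of variation 1 and mean EUR 10,000, 20,000 or 40,000. QALYs were assumed normal with mean/SD 0.2/0.4, 0.5/0.6 or 1.8/0.6. The first two QALY settings represent change in utility, as the Quality of life section describes; the third represents total QALYs. The threshold of EUR 12,274 appears in the Discussion, from a cited study, and serves only as an illustration; the other thresholds are assumed. Share of patients with NB < 0:

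| Willingness-to-pay (EUR) | All nine settings | Six change-based settings |
|---|---|---|
| 0 | 100% | 100% |
| 5,000 | 43-97% | 77-97% |
| 12,274 | 14-92% | 59-92% |
| 20,000 | 6-88% | 47-88% |
| 50,000 | 0.7-75% | 31-75% |
| 80,000 | 0.3-66% | 27-66% |

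Raising the threshold does not remove the problem. The share falls only towards P(E <= 0), which is Phi(-0.2/0.4) = Phi(-0.5) = 31% in the first QALY setting and Phi(-0.5/0.6) = Phi(-0.83) = 20% in the second.

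**5. Break-even from treatment cost alone.** The Format section puts protocol treatment at about 167 hours. At an assumed EUR 50-150 per hour this is 167 x 50 = EUR 8,350 to 167 x 150 = EUR 25,050. A patient who gains 0.5 QALY then has negative net benefit below W = 8,350/0.5 = EUR 16,700, or below 25,050/0.5 = EUR 50,100.

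**6. Effect of shifting.** With a constant k added, a log model compares the means of log(NB + k). Back-transformed, these are geometric means, and the comparison changes with k. A gamma model with identity link does estimate arithmetic means, and k cancels from a simple arm difference. However, k still has to be chosen, and it enters the assumed relation between variance and mean.

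**The case against.** The strongest reply is that nothing is fixed. The two families follow an e.g., the choice is left to the data, and the section's opening paragraph calls all its methods illustrative. A data-led choice could not quietly settle on an unshifted gamma or log-normal: the fit would fail at the first run, as it did above, and the analyst would turn to something else. A Gaussian model is already permitted. This stands and limits the severity. It does not make the examples suitable, and the text does not say what happens to negative values.

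Several stronger readings are tempting, but the document does not support them:

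- **That the trial will use gamma or log-normal.** It does not commit to either.
- **That every patient is negative at the low end of the acceptability curve.** This is exact only at or very near zero, and the range has no stated lower limit.
- **That the share can be read from the Background, where "more than one-third of the patients did not achieve a reliable change in BPD symptoms or even showed an increase in BPD severity".** This comes from earlier studies and mixes worsening with improvement too small to be reliable. Being a more-than figure, it gives no numerical upper bound either. It shows only that non-benefit is to be expected.
- **That different thresholds would be analysed with different models.** The section speaks of one model and one distribution, so this is speculation.
- **That arithmetic means are lost under both families.** This applies to log-transformation, not to a gamma model with identity link.

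**Conclusion.** The point holds in limited form. The only distributions offered as examples for net benefit cannot hold the variable that the same section defines. This follows from the definition, for any analysed patient with positive cost and zero or negative benefit, and needs no assumption about amounts.

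How many patients are affected is not documented. It ranged from 0.3% to 97% over the assumed settings with a positive threshold, and was at least 27% in every change-based setting up to EUR 80,000. Those figures rest wholly on assumed costs, QALY distributions and thresholds.

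Severity is minor to moderate. The flaw lies in one parenthesis, it concerns the economic objective and not the primary clinical outcome, and the announced update can correct it before any data are analysed.

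**What to change.** In the protocol update announced under Statistical analyses:

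1. Delete gamma and log-normal as examples for net benefit, and keep them for costs only.
2. Prespecify one model, used at all willingness-to-pay values, that admits negative values. Two options would serve:
   - a Gaussian multilevel model of net benefit with bootstrap intervals, resampling patients within centre and arm;
   - a joint model of cost and effect (for example gamma with log link for cost) with the same centre structure, from which mean net benefit and the acceptability curve are derived.

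The cost is a reworded sentence or two, standard bootstrap code and a little extra analysis work. Data collection does not change.

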### Additional substudies

Several secondary studies will be conducted, including, but not limited to, the investigation of the heterogeneity of BPD and substance abuse among BPD patients, a qualitative study into the perspectives of patients and therapists, and psychometric evaluations. First, BPD is characterized by considerable heterogeneity [165, 213]. Over the past years, researchers have attempted to identify BPD subtypes based on different indicator variables (e.g., DSM-5 criteria, interpersonal characteristics, temperament) and different statistical strategies (e.g., exploratory factor analysis, Q-factor analysis, finite mixture modeling) [214]. The BPD subtypes that emerged differed substantially between studies. According to Hallquist and Pilkonis [214], advances in classifying BPD subtypes can be made by using a theoretical model as guidance, for example Kernberg’s theory [215]. Therefore, a substudy into the heterogeneity of BPD will be performed based on theoretically justified indicators and state-of-the-art statistical methods.

A second substudy will focus on the co-occurrence of substance abuse and BPD. Research suggests that patients with BPD and substance abuse have more severe problems, including higher rates of suicide attempts, more treatment noncompliance, and increased risk of violence, compared to BPD patients without substance abuse (e.g., [216–218]). However, few trials have assessed the effectiveness of treatments for BPD patients with substance abuse. In addition, research into the effect of BPD treatment on substance abuse is also limited [219]. Third, qualitative research will be conducted to explore the perspectives of patients and therapists in key areas, including predictors, mechanisms of change, the treatments, and the implementation of the results in clinical practice. Finally, psychometric evaluations of several Dutch questionnaires (e.g., Dialectical Behavior Therapy-Ways of Coping Checklist, Ultrashort BPD Checklist) will be performed.

## Discussion

This article described the study protocol of a multicenter RCT focusing on the (differential) treatment effectiveness of DBT and ST for patients with BPD. The primary aim of the study is to improve treatment outcome of DBT and ST for BPD patients by optimizing treatment selection through identifying patient characteristics that specify which patients will benefit most from which treatment. In addition, we aim to elucidate the change mechanisms of DBT and ST, which is crucial for improving treatments and, in turn, treatment response [51, 52, 220]. Finally, the comparative effectiveness and cost-effectiveness of DBT and ST will be compared.

This trial provides a unique opportunity to gain more insight into one of the main questions dominating the psychotherapy research agenda: “What works for whom and why?”. Although DBT and ST share some important characteristics, different interventions related to different assumed core deficits in BPD are provided [58]. As each treatment provides a different therapeutic milieu and focuses on different goals and tasks, a particular treatment may be a better fit with some patients compared to others [45]. In this study, patient characteristics of (differential) treatment response will be identified and individual treatment recommendations (DBT or ST) will be generated. In addition, for each patient, an estimate will be provided of the potential advantage in symptom relief that might be gained in case the patient was allocated to his or her indicated treatment. Moreover, the potential advantage in other outcomes, for example functioning and cost-effectiveness, will also be estimated. Knowing which treatment is most cost-effective for whom may lead to more efficient allocation of healthcare resources, which is important, as the current healthcare system is characterized by constraints in resources (e.g., people, time, budget; [221]). However, before a treatment selection procedure can be implemented in clinical practice, replication and external validation of the prediction model is needed. Subsequently, a prospective study in which the patient and clinician collaborate in selecting the optimal treatment (i.e., shared decision making; [222]), guided by treatment recommendations based on the prediction model, should be conducted to evaluate the advantage of a treatment selection procedure. By using a state-of-the-art approach, the results of the current study can serve as the starting point for future studies into personalized medicine among BPD patients, and is therefore of great importance.

In addition, this trial provides insight into the comparative (cost-)effectiveness of DBT and ST. Although the effectiveness of both treatments has been established, DBT and ST have not been directly compared. Therefore, and because outcome measures differ substantially between studies on the effectiveness of DBT or ST, hypotheses concerning the differential effectiveness can hardly be formulated. According to the “Dodo Bird effect” [223, 224], all evidence-based psychotherapies are equally effective, suggesting that DBT and ST will produce equivalent outcomes. However, a meta-analysis into the comparative effectiveness of evidence-based treatments for personality disorders demonstrated that some treatments may be more effective than others [225]. In addition, Fassbinder et al. [226] hypothesized that ST may be more effective than DBT in reducing psychiatric comorbidity and improving quality of life, while DBT may lead to a better and faster reduction in self-harming and suicidal behaviors. Moreover, although not assessed in direct comparison with ST, the meta-analysis of Storebø et al. [25] into psychological treatments for BPD indicated that DBT may be especially effective for BPD-severity, self-harm, and psychosocial functioning. They also pointed out that more research into the effects of BPD-tailored treatments, including head-to-head comparisons, is needed. By focusing on an array of outcomes, this study will extend our knowledge on the potential differential effects of DBT and ST.

This study has several strengths. First, this RCT is quite inclusive in terms of patient characteristics, and as such designed to reflect clinical practice to enhance ecological validity. Second, this trial is conducted by a research group including researchers with balanced allegiance to either ST or DBT and an independent researcher (i.e., [name]), to prevent the potential effect of research allegiance on treatment outcomes [227]. Third, we adopt a broad view on treatment response by including outcome measures reflecting different areas of recovery (e.g., BPD symptoms, functioning, well-being). Focusing on outcomes beyond symptom reduction is in line with patients’ view on recovery [76, 77]. In addition, it follows a multi-method assessment approach, as the outcome measures include both self-report questionnaires and semi-structured interviews. Fourth, we include a large amount and broad range of patient characteristics potentially predictive of (differential) treatment response across DBT and ST. Finally, the presumed mediators and outcomes will be frequently measured on multiple time points during the treatments and mediation analyses will be performed by using state-of-the-art statistical analysis methods [228]. This allows us to establish concurrent as well as temporal relationships between the mediators and outcomes [228]. However, according to Lemmens et al. [229], understanding psychotherapeutic change may be too challenging, even in optimal research designs. Psychotherapy consists of a complex interplay of multiple mechanisms on different levels. Finding that a construct (e.g., therapeutic alliance) mediates treatment outcome does not explain *how* changes in this construct lead to changes in the outcome as it could involve several processes (e.g., cognitions, behaviors, emotions, neural systems) [63]. It is therefore highly questionable if these complex processes can be assessed by relatively simple mediational models. As such, this is one of the potential limitations of the current study.

This study has several other limitations that should be considered when evaluating the results. First, as power is conventionally set a 80% [84, 230–232], we used a minimum criterion of 80% power for the power analyses. However, this means that we accept a 20% chance of a false negative result. Second, since DBT and ST are both evidence-based treatments for BPD, differential effects in treatment outcome may be small or non-existing. To demonstrate equivalence or small effects between treatments, a very large sample size is needed. The sample size of the current study is not large enough (i.e., does not have ≥80% power) to reliably detect a small differential treatment effect. However, the comparison of treatments is not the main aim of the study. In addition, according to Luedtke et al. [233], a sample size of at least 300 patients per condition is required to have sufficient power for applying multivariable prediction models. Nonetheless, they also noticed that a smaller sample size might be justified if studies are designed to develop prediction models that can be tested in future studies. Moreover, the results of this study can contribute to building a database including trials on BPD that can be analyzed with meta-analytic techniques.

Second, this study does not include a no treatment control group, which might affect internal validity. When improvements are found in both treatments, but no significant differences between the treatments, the absence of a control group implies that it cannot be ruled out that non-specific factors such as attention or time (maturation) caused the improvements. However, including a control group receiving no treatment would clearly be unethical (e.g., patients are at risk of suicide). For similar reasons, it is not possible to standardize medication use and crisis management sessions. Any additional treatment or medication use will be monitored and included in the analyses.

Third, one of the treatment elements of DBT is out of office hours between-session (telephone) consultation by the individual therapist. The targets of telephone consultation include, among others, reducing self-harm and suicidal behavior and teaching patients how to apply learned skills in everyday life in order to encourage skills generalization [19]. In the current study, some centers provide 24/7 access to telephone consultation by the patient’s individual therapist, while the other centers provide telephone consultation within the limitations of the individual therapists, or within working hours. In case of emergency, the standard emergency procedures of each center will be followed. Although outside of office hours availability is considered to be an essential element of DBT by some authors [113, 234], the link between telephone consultation and outcome in DBT has not been evaluated [95, 235]. There is some preliminary support for the importance of telephone consultation [236]. However, studies into the effectiveness of DBT that did not apply 24-h telephone consultation by the individual therapist have found positive outcomes (e.g., [235, 237]). Van den Bosch and Sinnaeve [238] studied treatment programs of 25 DBT teams in the Netherlands. They found that only 36% of the DBT teams applied telephone consultation according to the guidelines of DBT. It can therefore be concluded that the current study is a good reflection of clinical practice, which enhances generalizability of our findings. Notwithstanding, we will monitor between-session (telephone) consultation within centers and examine potential effects.

Fourth, in this study, a component of treatment integrity (treatment adherence) will be assessed, which is, surprisingly, not standard procedure in trials investigating BPD treatments [25]. However, treatment integrity also constitutes of treatment differentiation and therapist competence [110]. Treatment adherence and treatment differentiation are closely related, in contrast to treatment adherence and therapist competence [239]. Treatment adherence represents a quantitative aspect of treatment integrity (i.e., how frequently a therapist utilizes prescribed techniques and procedures and avoids proscribed techniques and procedures), while competence represents a qualitative aspect (i.e., how well prescribed techniques and procedures are implemented) [109]. Adherence does not necessary presuppose competence; even with adequate adherence, therapists may deliver the treatment in an incompetent manner. The absence of competence ratings may threaten the validity of our results [109]. Moreover, treatment adherence will be assessed by trained master psychology students, whereas for DBT, adherence ratings by reliably trained therapists are considered the gold standard [240, 241]. However, students will receive a training from experienced therapists.

Fifth, it is a subject of some debate whether the EQ-5D is a valid instrument to measure quality of life in BPD patients, which can affect the economic evaluation [81]. According to Brazier [242], the EQ-5D might not measure what matters to patients with psychiatric disorders. In addition, in a cost-effectiveness study among BPD patients, van Asselt et al. [79] found contradictory results on the incremental risk ratios when recovery was based on the EQ-5D compared to the BPDSI-IV. In contrast, adequate responsiveness of the EQ-5D has been found in a BPD sample [243]. In addition, Soeteman et al. [244] concluded that the EQ-5D is sensitive to changes in the health status of patients with cluster B personality disorders. In addition to the EQ-5D, quality of life will be assessed by a recently developed instrument specially developed for patients with mental health problems (MHQoL-7D; [197]). The validation of this instrument is currently in progress, but preliminary results are promising [197]. Another point for consideration is that conclusions with regard to the most cost-effective treatment choice can be affected by the amount the society is willing to pay for an additional unit of effectiveness (i.e., willingness-to-pay threshold). Soeteman et al. [244] concluded that outpatient psychotherapy for cluster B personality disorder patients is the optimal treatment choice in case society is not willing to pay more than €12.274; otherwise, day hospital psychotherapy was the optimal treatment choice. To date, there is no consensus about reasonable willingness-to-pay thresholds, although guidelines have been proposed by the Dutch healthcare authority [245]. We will therefore calculate the probability of each treatment being cost-effective for different willingness-to-pay values. As a result, the optimal treatment choice can be different for different willingness-to-pay values.

Finally, this study is conducted during the COVID-19 pandemic. The COVID-19 pandemic has significant disrupted effects on society and is related to increased burden of mental health among individuals with mental disorders [246, 247]. Moreover, some authors suggest that patients with severe psychopathology, including BPD, may be especially at risk for symptom deterioration [247, 248]. In addition, some patients will temporarily receive treatment via videoconferencing in case face-to-face treatment is restricted in mental healthcare centers. Research on the effectiveness of online individual psychotherapy has found positive effects for several mental health disorders, including PTSD [249], anxiety disorders [250], and depression [251]. However, research on the effectiveness of online group psychotherapy is scarce [95, 252]. Consequently, we will control for a potential effect of the COVID-19 pandemic in the analyses.

